#### Extension Study: Months 6, 9, and 12 Visits (±1 Week)—If Participating in Optional Extension Study

Participants entering the optional extension may attend follow-up visits at month 6 (week 24 ±1 wk), month 9 (week 36 ±1 wk), and month 12 (week 52 ±1 wk). At the month 6 and month 9 visits, participants will verbally confirm their willingness to continue. Changes in concurrent medications and any AEs since the previous visit will be recorded at each visit. A researcher will assess the 28-joint tender and swollen joint counts and the patient and physician visual analog scales. CRP results obtained through routine clinical care will also be recorded to calculate the DAS28-CRP. Participants will complete the HAQ-DI and a paper RA-FQ unless they have completed the online RA-FQ within the preceding 24 hours.

A clinically confirmed flare will be defined as a DAS28-CRP of ≥2.4 and/or at least 1 swollen joint attributable to inflammatory RA activity. Confirmed flares will be managed by the ROADMAP clinical team as part of routine care, and the study investigator will record the estimated date of flare onset. At each visit, completed paper questionnaires and Axivity AX6 devices from the preceding monitoring period will be collected. Participants who do not wish to continue at month 6 or month 9 will complete the wearable usability and acceptability questionnaire and exit the study. All participants remaining in the study at month 12 will complete the questionnaire and exit the study. No participant will be followed for more than 12 months from baseline. These optional extension visits will be implemented only after approval of the submitted ethics amendment and all required sponsor and site approvals.

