#### Ad Hoc Flare Visits (Throughout the Study)

Patients tapering their DMARDs in the ROADMAP clinic may request additional ad hoc visits outside the usual 3-monthly schedules if they suspect an arthritis flare. There is no limit to the number of ad hoc visits, although in practice only one ad hoc visit would usually be expected for a patient who experiences a flare. In these cases, the patient will contact the study team to report possible flare symptoms, and a study investigator will then contact the ROADMAP clinic administrative team to arrange a ROADMAP clinic appointment and book a study visit to coincide with it. At the start of the ad hoc visit, patients will be asked to verbally confirm their willingness to continue in the study. Any changes in concurrent medications and any AEs since the last clinic visit will be recorded. A researcher will then assess the 28 joint tender and swollen counts, patient visual analog scale, and physician visual analog scale required for DAS28-CRP disease activity assessment. CRP blood test results obtained during routine clinical care at the ROADMAP clinic visit will also be recorded for DAS28-CRP calculation. The patient will then complete an HAQ-DI questionnaire and an RA-FQ paper questionnaire, unless an online RA-FQ has already been completed within the previous 24 hours.

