If arthritis flare is confirmed, defined as a DAS28-CRP of at least 2.4 or at least 1 swollen joint, this will already have been treated appropriately during the concurrent ROADMAP clinic appointment. The study investigator will record the estimated date of flare onset, and follow-up in the main study period will be terminated if not already completed. Patients who are not already enrolled in the optional 12-week extension study will be offered enrollment. If they agree, they will immediately enter the extension phase, any paper questionnaires and Axivity AX6 devices from the last visit will be collected, and they will be provided with 3 new Axivity AX6 devices and 1 wrist strap to wear for 28 days each in sequence on the nondominant wrist, or the dominant wrist if needed. If they cannot access the online REDCap portal, they will also be given 12 additional paper RA-FQs to complete weekly, and their next study visit will take place in 12 weeks according to schedule 6.3, replacing the planned week 12 main study visit. If the patient is already enrolled in the optional extension study, they will be given a feedback questionnaire on AX6 usability and acceptability, will continue wearing the AX6 monitors and completing any provided paper RA-FQs for the remainder of the ongoing 12-week extension period, and will then exit the study without an extension week 12 review to avoid an extra visit outside the ROADMAP clinic schedule; they will also be given a stamped addressed envelope to return the AX6 monitors and paper questionnaires by post. If a patient with confirmed flare declines the optional extension study, they will exit the study at that visit, any paper questionnaires and AX6 devices from the last visit will be collected, and they will be given a feedback questionnaire on AX6 usability and acceptability together with a stamped addressed envelope for postal return to the study team. If arthritis flare is not confirmed, the patient will continue to wear the Axivity AX6 monitors and complete RA-FQs according to the current schedule and will attend the next study visit as already arranged.

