### Adverse Events and Serious Adverse Events

#### Adverse Event

An AE is defined as any untoward medical occurrence experienced by the patient during their participation within the study. The severity of AEs is defined as follows:

Mild: Symptoms noted but no disruption to normal daily activitiesModerate: Symptoms sufficient to disrupt normal daily activitiesSevere: Symptoms sufficient to prevent normal daily activities

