##### Safety Outcomes

Safety outcomes, including AEs and SAEs, will be tabulated by type and severity, with the number and proportion of participants affected and the total number of occurrences reported.

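### After a flare confirmed at an ad hoc visit in the extension, device wear continues to an exit without review, so non-serious adverse events and medication changes in that window may be under-ascertained

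*Protocol article*

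**What the plan says.** All references are to the protocol article.

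- **Wear and exit (Ad Hoc Flare Visits).** A participant already in the extension whose flare is confirmed at an ad hoc visit "will continue wearing the AX6 monitors and completing any provided paper RA-FQs for the remainder of the ongoing 12-week extension period". The participant "will then exit the study without an extension week 12 review to avoid an extra visit outside the ROADMAP clinic schedule".
- **What comes back (same section).** At the flare visit the participant receives the usability questionnaire, and "they will also be given a stamped addressed envelope to return the AX6 monitors and paper questionnaires by post". No AE or medication form is named.
- **When AEs and medication changes are asked about.** For extension visits: "Changes in concurrent medications and any AEs since the previous visit will be recorded at each visit". For ad hoc visits: "Any changes in concurrent medications and any AEs since the last clinic visit will be recorded". The Month 3 Visit section has the same backward-looking question.
- **Period in which an event counts (Adverse Event).** An AE is "any untoward medical occurrence experienced by the patient during their participation within the study".
- **Reporting (Reporting AEs and SAEs).** All AEs go on case report forms, and site staff report any serious adverse event (SAE) to the chief investigator at once. Neither rule is tied to a visit.
- **Tabulation (Safety Outcomes).** AEs and SAEs are tabulated by type and severity, "with the number and proportion of participants affected and the total number of occurrences reported".

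**The concern.** The AE definition runs to the end of participation, but the described enquiry for this subgroup stops at the flare visit. Between the two the participant is still exposed to the study procedure, and the Causality section assesses AEs against exactly that procedure. A participant who was not asked will look the same in the safety table as one who had no event.

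The gap also falls at an awkward time. The Introduction says that treatment is changed after a flare and that short-term glucocorticoids may be used. Medication changes after the flare visit would help in reading the accelerometry from these weeks, and nothing is described that would collect them.

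Ascertainment would then differ between participants according to when and how their flare was confirmed.

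**Working it through.** **Step 1. Compare the flare routes.**

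| How the flare is confirmed | Wear afterwards | Later visit that asks about AEs and medication |
|---|---|---|
| Ad hoc, main period, extension declined | None; devices collected at that visit | Not needed |
| Ad hoc, main period, extension accepted | New 12-week period | Yes, a study visit 12 weeks later |
| Scheduled month 6 or 9 visit, participant continues | Until the next visit | Yes, at each later visit |
| Ad hoc, already in the extension | Rest of the 12-week period | None planned |

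In the first three rows, wear and enquiry end together. Only in the last does wear outlast the last planned enquiry.

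**Step 2. Check whether the window lies inside the AE period.** The ad hoc section puts exit after the remaining wear. The participant is therefore still in the study, and the AE definition applies throughout.

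**Step 3. Length of the window.** It is the remainder of a 12-week period: more than 0 and at most about 12 weeks. If flares fall evenly over the period (assumption), the mean is 12 / 2 = 6 weeks.

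**Step 4. Illustrative size.** The article gives no exposure figure to reproduce. From Target Recruitment Sample Size: 100 patients and a 50% flare rate, so 100 × 0.50 = 50 flares. The share confirmed at an ad hoc visit by someone already in the extension is not given, so a range is assumed.

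- Participants affected = 50 × share
- Mean participant-weeks = participants × 6
- Maximum participant-weeks = participants × 12

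| Assumed share of flares | Participants | Mean participant-weeks | Maximum participant-weeks |
|---|---|---|---|
| 10% | 5 | 30 | 60 |
| 25% | 12.5 | 75 | 150 |
| 50% | 25 | 150 | 300 |

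**Step 5. What cannot be computed.** The article gives no AE rate, so the number of events missed, if any, cannot be derived.

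**The case against.** The strongest case against the point is that the omission is deliberate and that other safeguards remain.

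- **SAEs and the general recording duty.** These rules do not depend on a visit, so a reader who inferred that no AE data are collected after the flare visit, or that SAEs cannot be reported, would go too far. Participants are not described as being routinely questioned between visits on any route. This stands. What this subgroup lacks is the later backward-looking question, and immediate reporting still requires the site to hear of the event.
- **Further ad hoc visits.** The article says "There is no limit to the number of ad hoc visits", and such a visit would look back over the window. This stands in part. These visits are requested by the patient for suspected flare, and the same section expects usually only one.
- **Undercounting.** A reader might infer that the safety table does undercount. The article does not show that: events up to the flare visit are recorded, no AE rate is given, and Protocol Specifications excludes joint pain, swelling, stiffness and fatigue from AE recording. Only a risk can be claimed.
- **The usability questionnaire.** It is handed over at the flare visit, but nothing requires it to be completed before the remaining wear, and it may come back in the envelope afterwards. No fault is claimed there.
- **A fuller protocol may hold the detail.** The reference to a schedule 6.3 suggests that one exists, and a call or form may be described in it. That is possible. But the article sets out this exit step by step, gives the reason for dropping the review and lists what is posted back, so on its face the procedure is complete without an enquiry.
- **Limited consequence.** The study is observational, safety is descriptive, and the primary outcome is time to first confirmed flare. This stands and limits the weight of the point.

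**Conclusion.** The point holds in a limited form. For participants already in the extension whose flare is confirmed at an ad hoc visit, the article leaves up to about 12 weeks of continued device wear inside the AE period with no planned enquiry about AEs or medication. Non-serious AEs, including device-related ones, and medication changes may be under-ascertained in that window, unlike on the other flare routes.

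The size is unknown. The range of about 30 to 150 participant-weeks rests on full recruitment of 100, a 50% flare rate, 10% to 50% of flares qualifying, an even spread of flares over the 12-week period, and all affected participants continuing to wear the device. The upper figure is the top of an assumed range, not an expectation. Neither a total absence of AE data nor an actual undercount is supported. Time to first confirmed flare is not affected.

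**What to change.** 1. In Ad Hoc Flare Visits, add a short AE and concurrent-medication form to the stamped envelope already provided, to be completed at the end of wear and returned with the monitors. Alternatively, have the study team make one phone call at the end of wear and record the same items.
2. In Safety Outcomes, state that AE ascertainment runs to the end of device wear for every participant.
3. If neither form nor call is adopted, state there instead that the reported safety period ends at the last study visit.

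The cost is one form in an existing mailing, or one short call per affected participant. No visit is added, so the article's reason for dropping the review is respected. The drawbacks are self-reported AEs and some non-return. The timing is favourable: 16 of the planned 100 participants had been recruited by July 1, 2026, and an ethics amendment on extended follow-up is already under review.

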### Patient Autonomy

Patients will have full autonomy throughout this study. The patient, informed of the full information as detailed in the patient information sheet, may withdraw their consent at any time. The wishes of the patient will be respected and would result in them exiting the study at that point. Any data collected up to that point would be retained and analyzed by the study team in line with the terms of the original patient consent form.

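### A first flare confirmed at an ad hoc visit during the extension leaves the pre-flare recording to a postal return, while the other confirmed-flare branches collect the devices in person

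*Protocol article*

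**What the plan says.** The section Ad Hoc Flare Visits gives three routes after a flare is confirmed.

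- Not yet in the extension, agrees to enter: "any paper questionnaires and Axivity AX6 devices from the last visit will be collected, and they will be provided with 3 new Axivity AX6 devices".
- Not yet in the extension, declines: "any paper questionnaires and AX6 devices from the last visit will be collected".
- Already in the extension: the patient "will continue wearing the AX6 monitors and completing any provided paper RA-FQs for the remainder of the ongoing 12-week extension period", "will then exit the study without an extension week 12 review to avoid an extra visit outside the ROADMAP clinic schedule", and "they will also be given a stamped addressed envelope to return the AX6 monitors and paper questionnaires by post".

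The section on the month 6, 9 and 12 extension visits states in-person collection: "At each visit, completed paper questionnaires and Axivity AX6 devices from the preceding monitoring period will be collected". A patient on the third route attends no further scheduled visit.

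Primary Analyses makes the first clinically confirmed flare the event and censors the others at the end of their own follow-up or at withdrawal. The model is updated weekly, uses all accelerometry up to each landmark, and predicts flare within the following 14 days. Missing Data fills gaps in accelerometry by last observation carried forward (LOCF).

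**The concern.** The same event, a flare confirmed with the patient on site, leads to two different ways of retrieving the data. The weaker one applies to patients whose first flare comes in the extension. Their current kit holds the recording that the primary model has to learn from and be tested on.

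Any loss would depend on outcome. Extension patients who stay flare-free and attend their next visit hand the devices over. Those with a flare confirmed ad hoc must post them after leaving the study. LOCF would then put older values in place of the missing days, so the gap would not show as missing, and some event patients would enter the model with data from well before their flare.

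Participants using paper RA-FQs would lose those weekly forms by the same route, which touches the combined model, although one RA-FQ is completed at the ad hoc visit itself.

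**Working it through.** **1. Retrieval by situation**

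| Situation | Devices in use returned |
|---|---|
| Ad hoc flare, not in extension, enters | In person, that visit |
| Ad hoc flare, not in extension, declines | In person, that visit |
| Scheduled extension visit, flare or no flare | In person, that visit |
| Ad hoc extension visit, flare not confirmed | In person, next scheduled visit |
| Ad hoc flare, already in extension | By post, after the period ends |

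Only the last row has no in-person handover.

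**2. Is it a primary event?** Yes, if it is the patient's first confirmed flare. A patient who entered the extension after a main-phase flare has already had the event and is not affected.

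**3. What the kit holds.** Three devices × 28 days = up to 84 days. Let the flare fall on day *d* of the current period. With weekly landmarks and a 14-day horizon, about 14/7 = 2 landmarks per flare have the event in their window, at roughly days *d* − 14 to *d*. If *d* ≥ 14, both lie within the current kit. If *d* < 14, part of the run-up is on the kit already collected at the previous visit. Days 14 to 84 make up 70/84 = 83% of the period, hence normally rather than always.

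**4. What LOCF would supply.** The last value available is from the end of the previous period. At those landmarks it is *d* − 14 to *d* days old, so 70 to 84 days old for a flare at the end of the period.

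**5. How many events?** The protocol gives no figure. As a formula:

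lost events = (first flares in the extension at full uptake) × uptake × share confirmed ad hoc × non-return rate.

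Illustration only. Assume 100 patients, a constant hazard with 50% flare by week 52, uptake 50–100%, ad hoc share 50–100% and non-return 10–30%.

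- Flare by week 12: 1 − 0.5^(12/52) = 14.8%. By week 24: 1 − 0.5^(24/52) = 27.4%.
- 12-month follow-up: 50 − 14.8 = 35.2 extension flares. Lost: 35.2 × 0.5 × 0.5 × 0.1 = 0.9, up to 35.2 × 1 × 1 × 0.3 = 10.6.
- 24-week follow-up: 27.4 − 14.8 = 12.6 extension flares. Lost: 12.6 × 0.5 × 0.5 × 0.1 = 0.3, up to 12.6 × 1 × 1 × 0.3 = 3.8.

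**6. What loss would do to the planned test.** Target Recruitment Sample Size gives N = 100 for AUC 0.8 against 0.6, 50% flare, 90% power and two-sided alpha 0.025. Hanley–McNeil variance: [A(1−A) + (n₁−1)(Q₁−A²) + (n₀−1)(Q₂−A²)]/(n₁n₀), with Q₁ = A/(2−A) and Q₂ = 2A²/(1+A). With 50 + 50 patients the SE is 0.0566 at A = 0.6 and 0.0445 at A = 0.8. Power = Φ[(0.2 − 2.241 × 0.0566)/0.0445] = 95.0%. The N needed for 90% power is 86 (90 with the Obuchowski variance). The stated 100 is not reproduced exactly, but it is sufficient.

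- Events dropped: 5 or 10 of 50 lost gives power of 93.3% or 90.8%.
- Events kept with stale values, assumed wholly uninformative (AUC 0.5) for a share *f* of events: AUC = 0.8(1−*f*) + 0.5*f*. For *f* = 5%, 10% or 20%, AUC is 0.785, 0.77 or 0.74 and power 89.7%, 82.0% or 60.4%.

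Under these assumptions, filling the gap by LOCF costs more than losing the same share of events.

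**The case against.** The protocol does name a return route, pays the postage, and explains why there is no closing visit: it wants no trips beyond the ROADMAP schedule. Address, telephone and email are taken at baseline, so returns can be chased. This is a choice about patient burden, in a study described as a development phase. All of that stands, but it does not defend leaving the used devices behind. The patient is already on site at the ad hoc visit, so collecting them there needs no extra trip.

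It also stands that the article does not say outright that finished devices go home again. That is inferred from post being the only route named in this branch, while both sibling branches state collection. That recordings sit on the device until collected is likewise implied rather than stated.

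Two stronger readings are not supported.

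- A reader might infer that wear after the flare serves no analysis and could simply stop. Primary Analyses compares predictions with patient-reported flare, and Secondary Analyses refits the models with patient-reported flare as the outcome. Neither states that follow-up ends at the first clinical flare, so later recordings may be used.
- A reader might see the same gap for patients who withdraw between visits. Patient Autonomy deals with keeping data already collected; device logistics at withdrawal are a detail that a condensed article may leave out.

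**Conclusion.** The asymmetry is in the text and affects primary events. For a first flare confirmed at an ad hoc extension visit, up to 84 days of recording, normally including the run-up to the flare, depend on a parcel sent after exit. Non-return would be confined to event patients and then masked by LOCF.

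The number of events at risk is unknown. A reader might take the top of the 12-month illustration, about 10 of 50, as an estimate. It is not one. It needs everyone to enter an optional extension, no extension flare to be confirmed at a scheduled visit, 12-month follow-up that Ethical Considerations says is still under review (6 months is approved), an assumed 30% non-return, and total loss for every affected event. Nor do the documents show that the study would be underpowered: dropping 10 of 50 events leaves 90.8%, and the lower figures under LOCF rest on stale values carrying no information at all. The case for change is that the loss would be outcome-dependent and is cheap to prevent.

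**What to change.** In Ad Hoc Flare Visits, amend the branch for patients already in the extension. When a flare is confirmed, collect the AX6 devices and paper RA-FQs used so far, as the other two branches do. Let the patient continue with the unused devices, or a replacement, for the rest of the 12-week period. Only that later recording then comes back by post. It is also worth reporting device return by flare status.

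The cost is a wording change and a replacement device for some patients. There is no extra visit, no change to clinical care and no change to the sample size. With 16 participants recruited by July 2026 and the longer extension still awaiting approval, most of the benefit is still available.

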### Patient Autonomy

Patients will have full autonomy throughout this study. The patient, informed of the full information as detailed in the patient information sheet, may withdraw their consent at any time. The wishes of the patient will be respected and would result in them exiting the study at that point. Any data collected up to that point would be retained and analyzed by the study team in line with the terms of the original patient consent form.

### Closure of the Study

Recruitment to the study will close upon recruitment of the 100th patient or on November 30, 2027, whichever is earlier. The end of the study is defined as the final visit of the last patient in the study.

